# The D*Phase-study: study protocol for a pragmatic two-phased, randomised controlled (non-inferiority) trial that addresses treatment non-response and compares cognitive behavioural therapy and short-term psychodynamic supportive psychotherapy for major depression

**DOI:** 10.1186/s12888-021-03156-8

**Published:** 2021-05-04

**Keywords:** Depression, Psychodynamic psychotherapy, Cognitive behavioural therapy, Prescriptive factors, Non-response, Working alliance, Allegiance, Treatment integrity

## Abstract

**Background:**

Several evidence-based psychotherapeutic treatment options are available for depression, but the treatment results could be improved. The D*Phase study directly compares short-term psychodynamic supportive psychotherapy (SPSP) and cognitive behavioural therapy (CBT) for Major Depressive Disorder (MDD). The objectives are 1. to investigate if, from a group level perspective, SPSP is not inferior to CBT in the treatment of major depressive disorder, 2. to build a model that may help predict the optimal type of treatment for a specific individual; and 3. to determine whether a change of therapist or a change of therapist and treatment method are effective strategies to deal with non-response. Furthermore (4.), the effect of the therapeutic alliance, treatment integrity and therapist allegiance on treatment outcome will be investigated.

**Method:**

In this pragmatic randomised controlled trial, 308 patients with a primary diagnosis of MDD are being recruited from a specialised mental health care institution in the Netherlands. In the first phase, patients are randomised 1:1 to either SPSP or CBT. In case of treatment non-response, a second phase follows in which non-responders from treatment phase one are randomised 1:1:1 to one of three groups: continuing the initial treatment with the same therapist, continuing the initial treatment with another therapist or continuing the other type of treatment with another therapist. In both treatment phases, patients are offered sixteen twice-weekly psychotherapy sessions. The primary outcome is an improvement in depressive symptoms. Process variables, working alliance and depressive symptoms, are frequently measured. Comprehensive assessments take place before the start of the first phase (at baseline), in week one, two and four during the treatment, and directly after the treatment (week eight).

**Discussion:**

While the naturalistic setting of the study involves several challenges, we expect, by focusing on a large and diverse number of research variables, to generate important knowledge that may help enhance the effect of psychotherapeutic treatment for MDD.

**Trial registration:**

The study was registered on 26 August 2016 with the Netherlands Trial Register, part of the Dutch Cochrane Centre (NL5753), https://www.trialregister.nl/trial/5753

## Background

According to estimates of the World Health Organization, 4.4% of the global population suffered from depression in 2015 [1]. Given the high prevalence of major depressive disorder and its severe impact on the functioning of patients who suffer from it, it is not surprising that depression is one of the three leading causes of the global disease burden [2]. Fortunately, several evidence-based pharmaco- and psychotherapeutic treatment options are available. Research suggests that most patients suffering from a psychiatric disorder prefer psychotherapy over medication [3]. Numerous well-conducted studies have demonstrated the effectiveness of several kinds of psychotherapy for MDD [4]. Although cognitive behavioural therapy (CBT) has been studied most [5, 6], there is no robust evidence indicating that efficacy varies between CBT and other evidence-based types of psychotherapeutic treatment for MDD such as interpersonal psychotherapy, behavioural activation, problem-solving therapy and psychodynamic psychotherapy [7–9]. The fact that the outcome estimates of different kinds of psychotherapy for MDD seem to be quite similar has led some people to argue that the effects of the different available psychotherapeutic treatment methods can mainly be attributed to common factors [10–12]. Common or non-specific factors are thought to be universal in all psychotherapy rather than specific to the particular method used. On the other hand, there are strong arguments against this common-factor hypothesis. See for a comprehensive overview Cuijpers, Reijnders and Huibers [13]. The presumed equivalence of different forms of psychotherapy therefore gives rise to an important debate about the possible working mechanisms underlying psychotherapy for depression.

The availability of so many different evidence-based psychotherapeutic treatments for depression that at least appear to yield comparable treatment results can nevertheless be viewed as a good thing. It means that there are several viable options available to which the therapist can resort if response is insufficient, particularly if one considers that both patients and therapists may have different preferences for particular types of treatment.

Worldwide, a substantial number of psychotherapists practise psychotherapy from a psychoanalytic perspective [14, 15]. The first major objective of the present study is to add to the evidence base for Short-term Psychodynamic Supportive Psychotherapy (SPSP) [16, 17]. SPSP is a specific form of psychodynamic psychotherapy that has been tested in several RCTs in the Netherlands [18] and was found to be non-inferior to Cognitive Behavioural Therapy (CBT) for patients with major depressive disorder [19]. The first part of the study consists of an RCT in which patients are randomly assigned to Short-term Psychodynamic Supportive Psychotherapy (SPSP) or Cognitive Behavioural Therapy (CBT).

The empirically established overall effectiveness of psychotherapy does not imply that all patients will benefit from treatment. A meta-analysis of the treatment outcomes of evidence-based forms of psychotherapy estimates that the number of patients that does not respond (as defined by an improvement of 50% or more on any given self-report depression-severity scale) is substantial (52%), while 57 to 59% do not achieve full remission after one treatment option [4] (as defined by a cut-off score on a depression-severity scale [20]). This implies an improvement in the treatment results in psychotherapy for depression is urgently needed. But where to begin? The development of new forms of psychotherapy over the years does not seem to have made treatment more effective [21]. One cannot therefore expect this to be automatically changed by the introduction of SPSP as a new form of evidence-based treatment for depression. The proponents of the ‘common factor’ hypothesis would also recommend focusing more on researching and working on the optimisation of non-specific treatment factors.

Another important approach in the quest to improve the results of psychotherapy would be to focus on the possibility that patients with specific characteristics respond differently to specific kinds of treatment; in other words, to learn more about which type of works best for which patients [22, 23]. If a specific method turns out to work better for specific patients, this would indicate that the use of a particular method probably *does* matter.

### Personalised therapy using a personalised advantage index

Studies of the use of a PAI (Personalised Advantage Index) found that, if patients receive indicated treatment in accordance with the PAI, there is a relevant and significant difference in treatment effect [24–26]. In this approach, the effect of one kind of psychotherapy for a specific individual by comparison with another kind of psychotherapy is predicted on the basis of an algorithm that is developed using advanced statistical methods [25, 27]. However, the utility of algorithms in clinical practice has not been established because the models that predict the best possible treatment method for individuals in a specific sample have not yet been validated. A PAI can be built only by using data from an RCT comparing two active treatments [28, 29]. CBT and SPSP are good candidates for a personalised predictive approach of this kind because they differ in several ways. They are located at either end of a spectrum with respect to the focus of therapy (symptom-centred to more person-centred). The stated mechanisms differ (for example, CBT is thought to change maladaptive cognitions and behaviours, whereas SPSP is thought to be more person-centred), as does the level of structure that is applied during the sessions (CBT is structured and SPSP is not). Lastly, only CBT uses homework assignments.

The second major objective of the study presented here is therefore to build a model that may help predict the optimal type of treatment for a specific individual.

### Non-response and therapy switch

At present, despite the prospect of improving treatment outcome if valid prediction models for personalised treatment selection become available, clinical practitioners are still faced with the difficult problem of patients not responding to treatment. Nevertheless, mainly on the basis of expert opinion rather than evidence, several guidelines for the treatment of depression provide recommendations for how to proceed in cases of non-response. For instance, in the United States, the advice of the American Psychiatric Association in its practice guideline for the treatment of patients with major depressive Disorder [30] is to intensify psychotherapy; to consider a switch to another psychotherapy; or switching to or adding antidepressant medication. The recommendations in the Dutch [31] guidelines are confined to switching to another kind of psychotherapy or antidepressant medication. The United Kingdom guidelines of the National Institute for Health Care and Excellence advise combining treatments (antidepressant medication and CBT) after initial non-response [32]. One recent study does indeed conclude that adding antidepressant medication or CBT to initial monotherapy (CBT or medication) leads to an increased response rate [33]. However, there is no research that supports the advice to switch to another type of psychotherapy when the patient prefers continuing psychotherapy [34]. A switch of therapy may require a switch of therapist because the initial therapist does not have the necessary expertise, but possibly also because a change in clinical stance is necessary, which could be less credible if delivered by the same person [35]. In line with the claims made by the advocates of the common-factor theory, the switch to another psychotherapist could in itself make a positive treatment response more likely. The patient could, for example, benefit from a change and establish a better working alliance with a new psychotherapist.

To our knowledge, the study presented here is the first to include a second treatment phase for non-responders to psychotherapy for MDD that addresses the possible effect of a switch of type of psychotherapy *and* therapist. Non-responders to therapy from the first treatment phase are randomised to three different groups (continuing with the same therapist and the same therapy, switching to another therapist for the same therapy, and switching to another psychotherapist and the other therapy). The third and last major objective of this study is to determine whether a change of therapist or a change of therapist and treatment method are effective strategies to deal with non-response. If the second of these two different strategies proves to be most effective, this could also serve as additional evidence for the relevance of the specific method used. At the least, knowledge about the effectiveness of different psychotherapeutic strategies to deal with initial treatment non-response can be expected to help improve treatment outcome. Even if the strategies studied fail to show any effect, then it will at least be clear that it might be best to switch to a different treatment modality altogether.

### The role of the working alliance

A minor objective of the D*Phase study will be to focus on the relevance of the therapeutic alliance as a predictor for treatment outcome. The alliance is commonly defined as the emotional bond established in the therapeutic dyad and the agreement between the therapist and patient about the goals of therapy and the steps necessary to achieve them [36]. The alliance has been repeatedly shown to be both positively and significantly correlated with treatment effect in different treatment methods [37]. This has often been interpreted as evidence that the therapeutic alliance is an important “common factor”. However, good alliances may just as well be the *result* of changes in symptoms (particularly early changes), rather than a cause [38]. Causal inferences can only be made if the mediator (in this case, the therapeutic alliance) *precedes* the treatment effect. There is a scarcity of methodically robust studies that meet this temporality criterion [39].

This study will therefore focus on a number of questions relating to the effect of the working alliance on treatment effect. To start with, how do symptom changes affect the working alliance? Does early symptom change predict the quality of the working alliance as perceived by the patient? And does the alliance also have an effect on symptom change in itself, as the common factor theory predicts?

In addition, there are other questions concerning the possible influence of the alliance. For example, does the alliance depend on the characteristics of the therapist, the patient or the match between them [38, 40–42]? The present study also represents a unique opportunity to examine whether, in the case of treatment non-response after treatment phase one, the effect of a switch of therapist or the switch of therapist *and* treatment method is mediated by a change in the therapeutic alliance. Should this be the case, that finding can serve as evidence that the quality of the therapeutic alliance is a causal factor in achieving good treatment outcomes.

### Treatment integrity and allegiance

Finally, in the quest to identify the factors that are the most relevant targets for the purposes of improving the outcomes of psychotherapy, this study will also focus on the concepts of treatment integrity and allegiance since therapist-related factors may also play a role in the treatment effect.

*Treatment integrity* consists of two factors: the therapist’s ability to apply therapy-specific techniques as intended (quality or competence) and the extent to which these techniques and methods are applied (quantity or adherence) [43–45]. A recent meta-analysis [46] of the influence of adherence and competence on treatment outcome across a wide range of mental disorders shows that adherence and competence generally have no significant effect. However, studies that specifically focus on the treatment of depression have found that the competence of the practitioner had a modest effect and reported a trend towards a positive effect of a larger degree of adherence.

The concept of *allegiance* is usually used in a scientific context, where it relates to the loyalty of a principal investigator to a specific treatment method [47]. In the current study, we will focus on the concept of allegiance as it relates to the *therapist* and its possible effect on the outcome of psychotherapy*.* There is only limited amount of empirical research into the effects of researcher allegiance on the outcome of RCTs, but meta-analyses indicate that allegiance has a clear effect on study outcomes [48]. It is plausible that, if allegiance affects the outcome of an investigation, similar effects will also be found in the treatment room [49]. The sparse experimental research that has been done may indicate that a therapist delivers treatment better when he or she has confidence in the particular type of therapy and when he or she is in favour of the underlying principles [50]. If this hypothesis is correct, it would certainly be worthwhile to investigate whether optimal matching between the indicated therapy and the practitioner who implements it could improve treatment results [51].

## Methods

### Design

Patient inclusion for this study began in September 2016. The study is a large RCT involving the direct comparison of two treatments (Short-term Psychodynamic Structured Psychotherapy; SPSP; and Cognitive Behavioural Therapy; CBT). Before the eight-week period of the first phase of treatment, subjects are randomly assigned 1:1 to two groups and are offered 16 twice-weekly sessions of SPSP or CBT. In the second part of the study, patients who respond inadequately to treatment (defined by < 50% improvement on a depression severity scale) are randomly assigned 1:1:1 to one of three conditions: 1. continuing the initial treatment with the same therapist (control group), 2. continuing the initial treatment with another therapist, and 3. a switch of method *and* therapist; for a maximum of another 16 twice-weekly sessions. A participant flowchart is presented in Fig. 1. At baseline, patients complete several questionnaires that assess potential predictive factors. During the treatment, patients are asked to complete questionnaires about depressive symptoms, the working alliance and perceived therapist characteristics at several time points. In case of response, patients are asked to fill in follow-up questionnaires in week four and eight after completing treatment phase one. An overview of measures at different time points can be found in Table 1.

**Fig. 1 Fig1:**
[figure not shown]
Participant flowchart

**Table 1 Tab1:** Overview of variables, measures and time points

		Time points (week)											
		Intake	Baseline	Treatment (phase 1) week				Treatment (phase 2) week				Follow-up (phase 1 responders) week	
**Variable**	**Instrument**			**1**	**2**	**4**	**8**	**1**	**2**	**4**	**8**	**4**	**8**
Psychiatric diagnosis	MINI	•											
**Outcome variables**													
Depressive symptoms (primary)	IDS-SR		•	•	•	•	•	•	•	•	•	•	•
Functional impairment	SDS		•				•				•		•
Well-being	MHC-SF		•				•				•		•
**Predictors**													
Demographic variables			•										
Traumatic life events (recent)	LTE		•										
Traumatic life events (lifetime)	LEC-5		•										
Psychological symptoms	BSI	•											
Agoraphobia	AGO		•										
Self-esteem	RSES		•										
Rumination	RRS		•										
Defence style	DSQ 40		•										
Personality organisation	IPO		•										
**Therapist & alliance**													
Therapist characteristics	CRF-S			•				•					
Working alliance	WAI			•	•	•	•	•	•	•	•		

### Power and sample size calculation

To calculate the required sample size for the first phase of the study we used the original dataset provided by the authors of a similar study which was conducted in a similar setting and population [19]. We expected this to be the best data available to make an accurate estimate of the standard deviation of the primary outcome needed to calculate the sample size.

The primary outcome measure of the current study is the severity of depressive symptoms as measured by the IDS-SR [52]. To test whether SPSP is in fact (as hypothesised) not inferior to CBT, a treatment that has already proven to be effective for treating MDD, we used the same non-inferiority margin (the maximum allowed difference in the mean outcome scores between the treatment groups to conclude that SPSP is indeed non-inferior to CBT) for continuous measures as Driessen et al. [19, 53] Accordingly, we adopted a non-inferiority margin of five points on the mean score on the IDS-SR immediately after treatment. This margin of a five-point difference between SPSP and CBT corresponds to a Cohen’s d of .30, which we assume to be a clinically acceptable difference. Power analysis for continuous outcomes [54] indicated that, to prove that SPSP is not inferior to CBT, 268 patients in total are needed for the first part of the study to provide 80% power in order to demonstrate that the lower limit of the one-sided 95% confidence interval (CI) will be above the non-inferiority limit of − 5 for the IDS-SR (1-β = 80%, SD = 16.42). Given the observed dropout rate of around 15% for the first 100 included patients, the aim is to include 308 patients for the performance of the per-protocol analysis.

Assuming that approximately 52% of the patients will be classified as non-responder after the first phase of study [4], we estimate that around 139 patients can be randomized across the three groups (1. same therapist, same treatment, 2. a switch of therapist only, 3. a switch of therapist and treatment) in the second phase of the study. According to a sensitivity analysis, by means of an analysis of covariance (ANCOVA), this suggests that we can significantly (α = .05) demonstrate a medium to large effect size (f = 0.35) with 80% power between the three groups in the second phase of the study.

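### Enrolling 308 with about 15% dropout leaves about 262 patients for the per-protocol analysis, slightly fewer than the 268 stated as needed

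*Protocol article*

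**What the plan says.** All the figures stand in the Protocol article under Power and sample size calculation.

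- **Required number:** "268 patients in total are needed for the first part of the study to provide 80% power". The inputs are a margin of five IDS-SR points, a one-sided 95% confidence limit and "1-β = 80%, SD = 16.42".
- **Dropout allowance:** "Given the observed dropout rate of around 15% for the first 100 included patients, the aim is to include 308 patients". The rest of that sentence says the target is meant to serve the per-protocol analysis.
- **Phase two:** about 139 non-responders are expected to be randomised again, on a non-response rate of 52%.

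The abstract repeats the target: "308 patients with a primary diagnosis of MDD are being recruited". The Statistical analysis section bases the non-inferiority conclusion on both the per-protocol and the intention-to-treat analyses.

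**The concern.** An allowance for dropout should give an enrolment figure that, after the expected loss, leaves at least the required number. If a fraction p is lost, enrolment must be the required number divided by (1 − p). Multiplying by (1 + p) always falls short, because (1 + p)(1 − p) = 1 − p², which is less than 1. At p = 0.15 that product is 0.9775, so about 2% of the required number is missing.

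The shortfall falls on the per-protocol analysis, for which the target was set and which is one of the two bases for the non-inferiority conclusion. The number 268 also has no slack: it is the smallest equal-arm total that reaches 80% on the stated inputs. As written, a reader will take it that 308 enrolled delivers 268 evaluable patients and 80% power. On the article's own dropout rate it does not.

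**Working it through.** **Inputs (Power and sample size calculation, unless noted).** Margin 5; SD 16.42; one-sided α = 0.05; power 80%; 1:1 allocation (abstract); required total 268; dropout around 15%; enrolment 308; non-response 52%. The true difference is not stated and is assumed to be 0. Dropouts are assumed to be lost from the per-protocol set equally in both arms.

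**1. Reproduce 268.** Per arm, n = 2(z₀.₉₅ + z₀.₈₀)² SD² / margin² = 2 × (1.645 + 0.842)² × 16.42² / 5² ≈ 133.4, rounded up to 134. The total is 268, an exact match. So 268 is a number to be analysed, before any allowance for loss.

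**2. Confirm from the text that 268 is the number after dropout.** 0.52 × 268 = 139.4, which is the article's 139. By contrast, 0.52 × 308 = 160.2. The phase-two estimate therefore takes 268 as the number remaining at the end of phase one.

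**3. Check the inflation.**

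| Calculation | Result |
|---|---|
| 268 × 1.15 | 308.2, matches 308 |
| 268 / 0.85 | 315.3, rounded up to 316 |
| 308 × 0.85 | 261.8, about 262 |
| 268 − 262 | 6 patients short |

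**4. Effect on power.** Without a covariate, power = Φ(5/SE − 1.645), with SE = 16.42 × √(2/n per arm).

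| Total analysed | SE | Power |
|---|---|---|
| 262 | 2.029 | 79.4% |
| 268 | 2.006 | 80.2% |
| 308 | 1.871 | 84.8% |

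With the noncentral t distribution, the first two rows become 79.2% and 80.0%. The loss is about 0.8 points either way.

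**5. Sensitivity to the dropout rate.**

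| Dropout | Left from 308 | Enrolment needed for 268 |
|---|---|---|
| 13% | 268.0 | 308.0 |
| 14% | 264.9 | 311.6 |
| 15% | 261.8 | 315.3 |

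The target and the requirement agree at a dropout of 1 − 268/308 = 13.0%, not at the stated rate.

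**6. Phase two.** 0.52 × 262 = 136.2, against 139.

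**The case against.** **The dropout rate is approximate.** The article says around 15%, seen in the first 100 patients. If that was 15 of 100, the 95% Wilson interval runs from about 9% to 23%, far wider than a gap of 6 patients can matter. At 13% dropout, 308 is enough. This stands as a reason not to treat 316 as a firm requirement. It does not reconcile the figures: 15% is the only rate given, and a higher true rate would widen the gap.

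**The planned analysis may recover the loss.** The primary analysis is an ANCOVA with baseline IDS-SR as covariate, and the stated calculation takes no credit for it. With variance multiplied by (1 − r²), a baseline–outcome correlation of r = 0.15 restores 80.2% power at 262. The documents give no r; over an assumed range, r = 0.2 gives 80.8%, r = 0.3 gives 82.6% and r = 0.5 gives 88.5%. This stands, and it is why any restated power should be labelled unadjusted. It does not make 308 × 0.85 equal 268.

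**Only one analysis set is affected.** With outcomes on all 308, power would be about 85%. This also stands.

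**The formula is not printed.** Multiplication by 1.15 is an inference from the match to 308.2. A reader might state it as fact, which the article does not allow. The inconsistency does not depend on it, since 308 × 0.85 is below 268 whichever formula was used.

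**Conclusion.** The concern holds as a minor arithmetic inconsistency. On the stated dropout rate, the enrolment target leaves about 262 patients for the per-protocol analysis, not 268. The cost is about 0.8 points of unadjusted power (79.4% against 80.2%) at one-sided 5%. This assumes a true difference of 0, the stated SD, and dropouts lost equally from both arms.

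Three stronger readings are tempting, and the documents do not support them:

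- **The trial is seriously underpowered because of this step.** A reader might read the 95% confidence interval in the Statistical analysis section as two-sided and compute 69.3% at 262. The same reading already gives 70.3% at the full 268, so dropout accounts for only 1 point. The sidedness of the interval is a separate question.
- **Phase two is compromised.** The article says around 139, and 136 is close to that. For three groups at α = 0.05 and 80% power, the detectable f moves only from 0.266 to 0.269.
- **Recruitment must rise to 316.** A power difference below 1 point, on an approximate dropout rate and before any gain from baseline adjustment, does not require it.

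**What to change.** Keep 308 and correct the statement of what it delivers. Under Power and sample size calculation, say that 308 enrolled with about 15% dropout is expected to leave about 262 patients for the per-protocol analysis. Say also that this gives about 79% power at one-sided 5% for a true difference of 0, before any gain from adjusting for baseline IDS-SR. For consistency, change the phase-two estimate from about 139 to about 136.

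The cost is a few words and a stated power about 1 point lower. The abstract's 308 can stand. No change to the design, recruitment or analysis is needed.

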### Randomisation

We use two potential moderators of outcome: severity (IDS-SR score < 39 or ≥ 39) and duration of depression (longer or shorter than 2 years) as stratification variables. Randomisation takes place using a system with closed envelopes in which the researcher is kept blinded to treatment allocation until the completion of the study phase and the patient is blind to the research condition until the start of the therapy. The therapist is given the information about the type of treatment to be administered shortly before the start of therapy.

Randomisation lists with an 1:1 allocation ratio were drawn up prior to the start of the inclusion of patients using an online tool [58]. Random block sizes are used. Block randomisation for phase two follows the same procedure as phase one, with an allocation ratio of 1:1:1. Patients receive a unique randomisation code that is linked to a unique patient number in the data file. The coding key is known to only one independent person. That person manages the data file that will be used for statistical analysis.

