#### The effect of therapist or therapy change after initial non-response

The effect of different follow-up treatment strategies, after an initial non-response to treatment (defined as an improvement of less than 50% over the initial measurement on the IDS-SR), on depressive symptoms, functional impairment and positive mental health will be analysed using multilevel repeated-measures linear-mixed modelling with group, time and group × time interaction as fixed factors.

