We therefore intend to implement a pragmatic, methodically strong, study in which the naturalistic setting will contribute to the generalisability of the results to everyday practice. This is a challenging undertaking and it also has certain limitations. Due to the naturalistic setting, for instance, it is not possible to control completely for the use of medication, although the use of medication is monitored and, if necessary, statistically controlled for in the analysis. Different treatment options for depression are available in the treatment centres and patients can choose a different kind of treatment offered by the treatment centre and refused to participate in the research project. This may result in a bias. Secondly, a double-blind design is never possible in a psychotherapy study because the therapist and patient are obviously aware of the kind of treatment that is being administered. However, by digitalising the administration of all the questionnaires that are used, both researchers and therapists are blinded to all patient-reported results and researchers are blinded to the treatment conditions. Thirdly, in spite of the fact that we include several potential predictors, one possible mediator and several moderators, there will certainly be important factors (latent and otherwise) that are not assessed in the current study. Lastly, because the study is primarily powered for the non-inferiority phase, it is expected that phase two of the study only has sufficient power to detect medium to large differences between the groups. Despite this relatively limited power, we still expect this phase of the study will generate meaningful observations on the effects of therapist and treatment switching.

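### The phase-two detectable effect of f = 0.35 does not follow from its printed inputs, which give about f = 0.27; the error is conservative and the correction minor

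*Protocol article*

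**What the plan says.** The figure is in the protocol article under Power and sample size calculation. Phase one is sized first: "268 patients in total are needed for the first part of the study to provide 80% power". The phase-two number is derived from that total. "Assuming that approximately 52% of the patients will be classified as non-responder after the first phase of study", the authors write, "we estimate that around 139 patients can be randomized across the three groups". The next sentence gives the method, "According to a sensitivity analysis, by means of an analysis of covariance (ANCOVA", and the result: at alpha .05 the study can "demonstrate a medium to large effect size (f = 0.35) with 80% power between the three groups".

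The Randomisation section confirms that phase two is allocated in blocks "with an allocation ratio of 1:1:1". The Discussion repeats the message as a limitation, saying that "phase two of the study only has sufficient power to detect medium to large differences between the groups". The article gives no covariate count, phase-two dropout, multiplicity correction or clustering allowance for the 0.35.

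**The concern.** A sensitivity calculation of this kind is fixed once the total number, the number of groups, alpha and power are given. All four are printed, so the detectable effect can be checked, and 0.35 looks too large for 139 patients.

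Phase two serves the third of the trial's three major objectives: what to do after non-response. This sentence is the article's only quantitative statement of what that phase can detect. If the figure is wrong, readers get a mistaken picture of the design's sensitivity. If it rests on assumptions that were left out, the printed description of the test is incomplete. In either case the number and its stated basis do not match.

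**Working it through.** **Inputs, all from Power and sample size calculation unless noted**

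- Total in phase two: 0.52 × 268 = 139.4, so about 139. This reproduces the article's own count.
- Groups: three, allocated 1:1:1 (Randomisation section), so numerator df = 2.
- Test: ANCOVA F test across the three groups, alpha .05, power 80%.
- Covariates: number not stated. One is used below, and 0 to 5 were tried.

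**Formula**

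Power = P(F′ > F_crit), where F′ is noncentral F with df1 = 2, df2 = N − 3 − covariates and noncentrality λ = f² × N. F_crit is the 95th percentile of the central F with the same df.

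**Attempt to reproduce f = 0.35**

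With N = 139 and one covariate, df2 = 139 − 3 − 1 = 135. For f = 0.35, λ = 0.35² × 139 = 17.03 and power is 96.3%. The article's 80% is not reproduced.

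**Solving the other way**

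- Detectable f at N = 139 and 80% power: 0.266, where λ = 0.2662² × 139 = 9.85. With 0 to 5 covariates it stays between 0.2662 and 0.2663.
- Smallest total with 80% power at f = 0.35: 82 patients (80.1%; 81 give 79.6%). Getting from 139 to 82 by attrition alone would need a loss of 1 − 82/139 = 41%.

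**Could another reading of the printed text give 0.35?**

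| Variant | Detectable f |
|---|---|
| N = 160 (0.52 × 308) | 0.248 |
| N = 136 (0.52 × 0.85 × 308) | 0.269 |
| N = 118 (139 less 15%; assumption, as the 15% is a phase-one rate) | 0.290 |
| N = 139, power 90% | 0.305 |
| N = 139, power 95% | 0.337 |
| N = 139, omnibus alpha .0167 | 0.305 |

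None of these reaches 0.35, and the last three contradict the printed power or alpha.

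**Could unstated allowances give 0.35?**

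For pairwise two-sided t tests at 80% power, with f = d/2 for two equal groups:

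| Per group | Alpha | d | f |
|---|---|---|---|
| 46 | .05 | 0.59 | 0.295 |
| 46 | .0167 (three comparisons) | 0.69 | 0.343 |
| 44 | .0167 (three comparisons) | 0.70 | 0.351 |
| 39 (15% loss) | .025 (two comparisons) | 0.71 | 0.355 |

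The last two rows come to 0.35 within about 0.005. They describe a different test from the one printed.

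**The case against.** The strongest reply is that the authors may have computed 0.35 correctly from assumptions that a condensed article dropped. The pairwise rows above show that this is possible: Bonferroni-corrected comparisons with some attrition give almost exactly 0.35. That stands, and it means one cannot say that nothing explains the figure or insist that 0.27 is the only right number. It does not rescue the sentence, which specifies alpha .05 and a comparison across all three groups.

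The second reply is that little depends on the figure. That also stands. The 139 is simply what phase one is expected to yield, and the Discussion says openly that the trial is powered mainly for non-inferiority.

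A reader might infer more than the documents support:

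- *That the Discussion's limitation is wrong.* It is not. On the conventional benchmarks for f (0.25 medium, 0.40 large), 0.27 to 0.29 still lies between medium and large.
- *That the planned "multilevel repeated-measures linear-mixed modelling with group, time and group × time interaction as fixed factors" contradicts the ANCOVA, or that missing pairwise detectable differences are a defect.* Powering on a simpler model than the one analysed is common. The choice of contrasts is detail that an article may leave to the full protocol or the SAP.
- *That the discrepancy can be put in IDS-SR points.* The only SD given, 16.42, was derived for the phase-one outcome. The documents give none for phase-two non-responders, and f in an ANCOVA is scaled to the covariate-adjusted residual SD.
- *That a null phase-two result would be misread because of this figure.* A null result is read from the estimate and its confidence interval, not from a planning value.

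**Conclusion.** The point holds as a reporting error. On its printed inputs phase two can detect f of about 0.27 rather than 0.35, and it has about 96% power for f = 0.35, an effect that would need only about 82 patients at 80% power.

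The direction is conservative, because the article claims less nominal sensitivity than its inputs imply. It is a minor correction and not a must-fix. The 0.266 rests on the stated total, groups, alpha and power, and on independent observations. It barely depends on the covariate count. Clustering by therapist, or allowances that were made but not printed, would raise the detectable effect, but the article claims neither for this figure.

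**What to change.** In Power and sample size calculation, do one of two things:

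1. Restate the detectable effect as f of about 0.27 for 139 patients. If an allowance for phase-two loss is wanted, add about 0.29 for 118 patients and label the 15% as an assumption carried over from phase one.
2. If 0.35 was obtained from further allowances, such as Bonferroni-corrected pairwise tests with attrition, state the test, the per-group number, the alpha and the dropout that produce it, in place of the present description of a three-group comparison at alpha .05.

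The Discussion sentence needs no change. The cost is one sentence of text, with no effect on recruitment, conduct or analysis.
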